## Abstract

**Background:**

Autosomal dominant polycystic kidney disease (ADPKD) is one of the most common potentially life-threatening inherited kidney diseases. It is the fourth most common cause of end-stage renal disease requiring renal replacement therapy. There are few management options for controlling disease progression. Hence, identification of alternative treatments for patients is important. The Chinese herbal *yinang* formulation (YNF), which is derived from a Chinese patent medicine, appears to have a satisfactory effect in treating ADPKD. Because a considerable proportion of ADPKD patients presenting with chronic kidney disease (CKD) stages III–IV are diagnosed with the spleen, kidney deficiency, and blood stasis syndrome according to the diagnostic criteria of traditional Chinese medicine (TCM), we hypothesize that YNF may be a complementary drug for ADPKD patients with the corresponding syndrome. Therefore, we have designed a strict clinical trial to evaluate the safety and efficacy of YNF for ADPKD patients with CKD stages III–IV exhibiting the TCM syndrome of spleen, kidney deficiency, and blood stasis.

**Methods/design:**

This is a multi-center prospective double-blind randomized controlled trial. The total target sample size is planned to be 72 participants, with a balanced treatment allocation (1:1). The experimental intervention will be YNF plus conventional therapy and the control intervention will be a placebo plus conventional therapy for 24 weeks. An additional 24 weeks of follow-up will be conducted after treatment completion. The primary outcome will be the estimated glomerular filtration rate (eGFR). Changes in total kidney volume (TKV), serum creatinine (Scr), blood urea nitrogen (BUN), TCM symptoms, and pain will be the secondary outcomes. Adverse events (AEs) will be monitored throughout the trial.

**Discussion:**

This study will be the first placebo-controlled randomized controlled trial to assess whether YNF plus conventional therapy has a beneficial effect on eGFR, TKV, Scr, and BUN, and whether it can alleviate TCM clinical symptoms, reduce ADPKD-related pain, and reduce the frequency of AEs for ADPKD patients with CKD stages III–IV with the spleen, kidney deficiency, and blood stasis syndrome. The results of this trial may provide an evidence-based recommendation for clinicians.

**Trial registration:**

Chinese Clinical Trials Register, ChiCTR-INR-16009914. Registered on 18 November 2016.

**Electronic supplementary material:**

The online version of this article (10.1186/s13063-019-3563-5) contains supplementary material, which is available to authorized users.

## Background

Autosomal dominant polycystic kidney disease (ADPKD) is one of the most common potentially life-threatening inherited kidney diseases. The incidence of ADPKD worldwide is about 1 in 1000 to 1 in 400 [1]. It is the fourth most common cause of end-stage renal disease (ESRD) requiring renal replacement therapy. It is characterized by accelerated cyst growth resulting in increased total kidney volume (TKV) and renal dysfunction [2, 3], and it affects more than 1.5 million people in China [4] and up to 12 million individuals worldwide [5]. ADPKD is a heterogeneous disorder with two genes identified: PKD1 and PKD2 [6]. The prevalence of autosomal *recessive* polycystic kidney disease is less common than ADPKD, but together with nephrophthaisis is the leading cause of ESRD in childhood [7].

Currently, there are few management options for controlling these diseases. Patients with ADPKD and renal failure are most commonly treated with hemodialysis. The treatment includes non-specific measures that are applicable to all ESRD patients, such as strict blood pressure control, dietary protein restriction, a low salt diet, and statins, which may prevent progression of the disease and reduce cardiovascular mortality [8]. Useful drugs in the management of ADPKD include small-molecule cystic fibrosis transmembrane conductance regulator (CFTR) inhibitors, mammalian target of rapamycin (mTOR) inhibitors, vasopressin V2-receptor (V2R) antagonists, and somatostatin analogues [9]. However, there are a number of limitations with those medications. V2R antagonists and newer agents inhibit pathological pathways in cyst formation. Several preclinical and clinical studies on the V2R antagonist tolvaptan reported evidence of its usefulness in ameliorating the decline of renal function over 1 year in later-stage ADPKD [10]. Since some questions and problems remain (e.g., hepatotoxicity, polyuria, polydipsia, no data on quality of life, and cost-effectiveness) [11], the use of tolvaptan requires careful consideration and balancing of benefits and risks [12]. The lack of specific treatment options for ADPKD makes it difficult for physicians and researchers working in nephrology.

Chinese herbal medicine has been used in the treatment of diseases for thousands of years in China. It is well known that traditional Chinese medicine (TCM) cures ailments based on syndrome differentiation, which is the main characteristic and therapeutic rule of TCM. Clinical information is gathered using the four main diagnostic TCM procedures (observation, listening, interrogation, and pulse-taking) and diagnosis follows TCM criteria. With our many years of clinical practice in the management of ADPKD, we have found that the main pathogenesis of ADPKD is spleen and kidney deficiency (soreness and weakness of the waist and knees, fatigue, cold or numbness of limbs, mental listlessness, lower limb edema, frequent night urination, and sunken pulse) combined with blood stasis (abdominal mass, pain or tingling in the back, subcutaneous petechia, squamous and dry skin, chest tightness, dark purple or dull red tongue with white fur, and strong astringent pulse). The clinical terms for these symptoms are those used in TCM for diagnosis and treatment. The national standard in China for this syndrome was published in February 1997 [13] and was verified by our previous work [14].

The *yinang* formulation (YNF) is derived from a Chinese patent drug originally designated for the clinical treatment of ADPKD patients diagnosed with the spleen, kidney deficiency, and blood stasis syndrome [14]. However, it is not clear whether YNF is effective for ADPKD patients with chronic kidney disease (CKD) stages III–IV. We hypothesized that for patients with ADPKD, YNF could improve the estimated glomerular filtration rate (eGFR), improve serum creatinine (Scr) levels, reduce TKV, reduce the blood pressure, improve symptoms and signs of CKD, reduce ADPKD-related pain, and reduce the number of adverse events (AEs). Thus, a multi-center prospective double-blind placebo-controlled randomized clinical trial was designed to evaluate the safety and efficacy of YNF for CKD stages III–IV in ADPKD patients.

### Aim of the trial

This clinical trial aims to disprove the null hypothesis that YNF granules in an oral dose of 36 g taken twice daily compared to a placebo does not improve the renal function of ADPKD patients at CKD stages III–IV with the spleen, kidney deficiency, and blood stasis syndrome.

## Methods/design

### Trial design

This is a multi-center randomized double-blind placebo-controlled clinical trial lasting 24 weeks. An additional 24 weeks of follow-up will be conducted after treatment completion. The design of the trial follows a strict scientific clinical research methodology and complies with principles of the Declaration of Helsinki and the guidelines for good clinical practice (Fig. 1).

**Fig. 1 Fig1:**
[figure not shown]
Patient flow in the YNF study for the intention-to-treat analysis. ADPKD autosomal dominant polycystic kidney disease, BID twice daily, TCM traditional Chinese medicine, TKV total kidney volume, YNF *yinang* formulation

### Sample size calculation

The sample size was based on the primary outcome of a change in baseline eGFR. To determine the sample size, we reviewed unpublished data for eGFR changes for 22 ADPKD outpatients at CKD stages III–IV. The mean value of eGFR was 26.71 mL/min/1.73 m^2^, and the standard deviation was 8.53 mL/min/1.73 m^2^. It was assumed that eGFR for the YNF group would be significantly higher than for the control group by more than 6 mL/min/1.73 m^2^ after 24 weeks. If α = 0.05 and the test efficacy 1 – *β* = 0.80, then the sample size$$ {n}_1=\kern0.5em \kappa {n}_2 $$

where$$ {n}_2=\frac{\left({\mathrm{Z}}_{\alpha /2}+{\mathrm{Z}}_{\beta}\right){}^2\kern0.5em \sigma {}^2\kern0.5em \left(1\kern0.5em +\kern0.5em 1/\kappa \right)}{\varepsilon^2}. $$

Thus, *n*_1_ = 64, with 32 in each treatment group. Considering a 10% dropout rate, the planned sample size for randomization was increased to 72. Participants will be randomly assigned in a ratio of 1:1. Each of the three participating hospitals will recruit 24 patients, 12 in the experimental group and 12 in the control group.

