### Outcomes

The primary outcome of this trial will be the eGFR using the CKD Epidemiology Collaboration formula [21]. Secondary outcomes include changes in TKV, Scr, blood urea nitrogen (BUN), TCM symptoms, and pain. A composite outcome looks at the incidence rates of all possible safety events between two groups. AEs will be monitored throughout the trial and several biological indicators (blood and urine tests, electrocardiograms, and liver function test) will also be closely watched.

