### Statistical analysis

A formal and detailed statistical analysis plan will be formulated before the database is locked. The baseline characteristics of both groups, such as gender, age, and smoking status, will be compared by either a χ^2^ test or Student’s *t*-test. Continuous variables will be presented as means ± standard deviations or medians, and differences in such variables will be analyzed using an independent *t*-test or the Wilcoxon signed-rank test. A repeated measurement of variance analysis model of these outcomes will be built.

The difference in eGFR will be tested using two-way ANOVA with repeated measures. Categorical variables will be expressed as numbers and percentages, and differences in such variables will be calculated and compared using a χ^2^ test and Fisher’s exact test. All statistical tests will be two-sided, and the level of significance will be set to *P* < 0.05. Multiple imputation will be used to handle missing data. All patients enrolled will be included in the primary analysis in accordance with the intention-to-treat principle. The statistical analysis will be performed in a blind manner by an independent statistician using SPSS (version 24.0, IBM, NY, USA). No additional analyses or an interim analysis are scheduled.

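### The sample size is said to rest on change in eGFR but uses the SD of eGFR level, so 80% power is not established for change or for the repeated-measures ANOVA named for eGFR

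*Protocol article*

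**What the plan says.** All of the sizing text is in the Protocol article, section Sample size calculation.

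- Outcome used for sizing: "The sample size was based on the primary outcome of a change in baseline eGFR".
- Source of the planning figures: "we reviewed unpublished data for eGFR changes for 22 ADPKD outpatients at CKD stages III–IV".
- Figures reported from that source: "The mean value of eGFR was 26.71 mL/min/1.73 m^2^, and the standard deviation was 8.53" (mL/min/1.73 m²).
- Assumed effect: "eGFR for the YNF group would be significantly higher than for the control group by more than 6 mL/min/1.73 m^2^ after 24 weeks".
- Error rates: "If α = 0.05 and the test efficacy 1 – *β* = 0.80". Statistical analysis adds: "All statistical tests will be two-sided, and the level of significance will be set to *P* < 0.05".
- Allocation: "Participants will be randomly assigned in a ratio of 1:1".
- Result: 32 per group, 64 in total, raised to 72 for 10% dropout.

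Two other sections bear on the point. Outcomes defines the endpoint without mentioning change or a time point: "The primary outcome of this trial will be the eGFR", calculated with the CKD-EPI formula. Statistical analysis names a two-way repeated-measures ANOVA for the difference in eGFR, and lists an independent t-test among the general methods for continuous variables.

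**The concern.** The paragraph names one quantity and uses another. A mean of 26.71 in patients at CKD stages III–IV can only be an eGFR level, so the 8.53 beside it is the between-patient SD of level. The SD of a 24-week change is a different quantity, which depends on how strongly a patient's two values are correlated. The repeated-measures ANOVA also depends on that correlation, and the calculation does not use it.

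This is the only justification of the sample size, and it concerns the primary outcome. If the 80% figure does not belong to the analysis that will be reported, readers do not know what difference the trial was able to detect.

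**Working it through.** **1. Reproducing the plan's figure.** Inputs from Sample size calculation: σ = 8.53, ε = 6, two-sided α = 0.05, power 0.80, κ = 1.

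n per arm = (1.960 + 0.8416)² × 8.53² × (1 + 1/1) / 6² = 7.849 × 72.76 × 2 / 36 = 31.73, so 32.

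Total 64; 64 / (1 − 0.10) = 71.1, so 72. The stated figures reproduce exactly, which confirms that the SD of level went into the formula. Power at 32 per arm is 80.3% by the normal approximation and 79.1% by the exact t-test.

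**2. What the 80% describes.** It is the power of a two-sample comparison of eGFR levels at week 24, without baseline adjustment, when the SD in each arm is 8.53 and the true difference is 6.

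**3. Carrying it over to change.** With equal SDs at baseline and week 24 and within-patient correlation ρ:

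SD of change = SD of level × √(2(1 − ρ)).

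This equals 8.53 only when 2(1 − ρ) = 1, that is ρ = 0.5. The protocol gives no ρ, so the values below are assumptions (level SD 8.53, difference 6, normal approximation).

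| Assumed ρ | SD of change | n per arm for 80% | Power at 32 per arm | Detectable difference at 80%, 32 per arm |
|---|---|---|---|---|
| 0.5 | 8.53 | 32 | 80% | 5.97 |
| 0.7 | 6.61 | 20 | 95% | 4.63 |
| 0.8 | 5.39 | 13 | 99% | 3.78 |
| 0.9 | 3.81 | 7 | >99% | 2.67 |

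Detectable difference = (1.960 + 0.8416) × SD × √(2/32) = 0.7004 × SD.

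Below ρ = 0.5 the error runs the other way: at ρ = 0.3 the SD of change is 8.53 × √1.4 = 10.09 and power is about 66%.

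**4. Uncertainty in the level SD.** An SD estimated from 22 patients has 21 degrees of freedom. Its 95% interval, assuming normality, is 8.53 × √(21/35.48) to 8.53 × √(21/10.28), or 6.56 to 12.19. For the unadjusted level comparison at 32 per arm, exact t-test power is about 95% at the lower limit and 49% at the upper.

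**5. A baseline-adjusted analysis, for comparison.** Residual SD = SD of level × √(1 − ρ²). With SD 8.53 and assumed ρ = 0.8 this is 8.53 × 0.6 = 5.12, and the detectable difference is 0.7004 × 5.12 = 3.58, about 3.6. If the level SD were 12 (assumed), the residual SD would be 7.20 and power for a difference of 6 about 92%.

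**The case against.** The best defence is that the calculation is coherent if the endpoint is the week-24 level. The effect is worded as a difference in eGFR between groups after 24 weeks, Outcomes defines the endpoint simply as eGFR, and an independent t-test is listed for continuous variables. A level SD paired with a level difference then fits. This stands: a reader might infer that the 80% matches no planned analysis at all, and that goes too far. It does not remove the problem, because the same paragraph says the sizing outcome is change and that change data were reviewed, and the test named specifically for eGFR is the repeated-measures ANOVA.

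It can also be said that using a level SD is conservative. That is true for change if the level SD is 8.53 and ρ exceeds 0.5, which is plausible but is not stated in the protocol.

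A mean of 26.71 may tempt a reader further, to conclude that the 22 outpatients were mostly at stage IV, that their SD is too narrow for entry at 15 to below 60, and that an even spread over that range (SD 45/√12 = 13.0, power 44%) shows the trial to be underpowered. The document does not support this. It describes the 22 as stages III–IV, the same stages as the trial, and gives no stage split. Any split would have to be derived from an assumed normal distribution, and an eligibility range does not mean enrolment fills it evenly. A wider SD in the trial is possible but not shown.

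**Conclusion.** The inconsistency is real: the section names change in eGFR but enters the SD of level. The figures 32, 64 and 72 are arithmetically right. The 80% power for a difference of 6 holds for an unadjusted week-24 comparison of levels with SD 8.53. It is not established for change from baseline, except at ρ = 0.5, or for the planned repeated-measures ANOVA.

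The direction of error cannot be fixed from the protocol. With level SD 8.53 and assumed ρ of 0.7 to 0.9, power for change is 95% or more; a larger level SD or a smaller ρ would reduce it. A reader might infer that the trial is underpowered, or that a null result could not be interpreted. Neither follows: the first depends on an SD and a correlation that are not given, and a null result would be read from the estimate and its confidence interval. This is a moderate point about a mislabelled planning input. It should be corrected, but it gives no reason to change the number of patients.

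**What to change.** Keep the sample size at 72 and rewrite the sample size paragraph to do three things.

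1. State whether the primary endpoint is eGFR level at week 24 or change from baseline to week 24, and use the same wording in Outcomes.
2. Name one primary analysis for it. Week-24 eGFR adjusted for baseline eGFR is preferable, since baseline eGFR is already scheduled at Visit 2. If the repeated-measures ANOVA is kept, the power statement should be derived for that model.
3. Restate power, or the difference detectable at 80% power with 32 per arm, using the SD that matches that analysis and showing a range of SD and ρ. An example entry is about 3.6 for a baseline-adjusted analysis at SD 8.53 and ρ = 0.8.

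The SD and correlation can come from the 22 outpatients, if their changes were in fact recorded. Otherwise they can come from the trial's own eGFR at Visit 1 and Visit 2, which are 24 weeks apart and both before treatment, so nothing is unblinded. Trial status does not show that all Visit 2 values were in hand, so these data should be used as they become available.

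The cost is one revised paragraph and a short calculation, with no added patients, visits or measurements.

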### Study setting and recruitment

This study will recruit 24 outpatients at each of three trial sites in Shanghai in mainland China: (1) Shuguang Hospital affiliated to Shanghai University of TCM, (2) Shanghai Changzheng Hospital affiliated to the Second Military Medical University, and (3) Shanghai Municipal Hospital affiliated to Shanghai University of TCM. Advertisements to encourage people to enroll in the clinical trial will be posted on the study's web page.

### Participants

The study plans to enroll 72 patients diagnosed with ADPKD at CKD stages III–IV and with the spleen, kidney deficiency, and blood stasis syndrome. To be enrolled in the trial, potential participants must satisfy the inclusion and exclusion criteria listed below.

### Diagnostic criteria for ADPKD

Participants are diagnosed with ADPKD based on a known family history, imaging features, or genetic testing. No distinction will be made between those with mutations of PKD1 or PKD2. For patients with ADPKD, eGFR is within the range 15 to 60 ml/min/1.73 m^2^. Patients have abnormal laboratory tests, and loss of renal structure and endocrine function for more than 3 months. It is an irreversible and chronic progressive disease [15].

### Diagnostic criteria for TCM syndrome differentiation

According to the *Guidelines for Clinical Research of Chinese Medicine (New Drug)* [16], a patient has to present with at least two of the primary symptoms and more than two of the secondary symptoms listed below to be diagnosed with the spleen, kidney deficiency and blood stasis syndrome.

Primary signs and symptoms:abdominal masssoreness and weakness of the waist and kneespain or tingling in the backfatiguecold or numbness of limbs

Secondary symptoms:mental listlessnesslower limb edemasubcutaneous petechiasquamous and dry skinchest tightnessfrequent night urinationdark purple or dull red tongue with white furweak, sunken, or strong astringent pulse

### Inclusion criteria

adult subjects with a diagnosis of ADPKD as stated above and with a TCM diagnosis of the spleen, kidney deficiency, and blood stasis syndromeaged 18–75 years15 mL/min/1.73 m^2^ ≤ eGFR < 60 mL/min/1.73 m^2^not receiving renal replacement therapynot suffering from chronic hepatitis, hepatic dysfunction, cardiovascular diseases, or any other life-threatening conditionsnegative urine or serum pregnancy test within 24 h prior to administration of YNF and agrees to use contraception throughout the study and for 6 months after

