### Randomization

The central randomization list was generated by an independent statistician using SPSS (version 24.0, IBM, NY, USA). Altogether, 36 patients will be assigned to the intervention group and to the control group using a balanced block randomization with 6 blocks. We will randomly select blocks of size 4. Telephone-based randomization will be performed at each coordinating center by an independent physician who is not engaged in recruitment, treatment, or assessment. Participants will be randomly assigned in each site to the YNF group and the placebo group in a ratio of 1:1. After screening, if the patient agrees to participate and voluntarily signs the informed consent form (Additional file 2), the independent physician in each trial site will sequentially assign a random number to them.

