### Measurement items and time points of data collection

Relevant examinations will be performed to collect patient data at 24 weeks before baseline, at baseline, every 4 weeks from 4 to 24 weeks during treatment, and an additional follow-up evaluation will be performed at visit 9 (48 weeks). General information collected will include name, age, gender, ID number, date of birth, home address, contact information, history of present illness, past medical history, family history, personal life history, menstrual history, marital history, allergy history, social history, physical examination results, and laboratory examination results.

There is evidence that age-related TKV can reflect the progress of ADPKD. An MRI scan can accurately measure renal blood flow and evaluate renal cyst compression, which is associated with pain, hypertension, hematuria, albuminuria, and loss of renal function. TKV combined with age and renal function can be used to evaluate the risk of progress to ESRD [19]. The T2 shortening imaging technique of MRI with no radiation damage, no use of gadolinium as a contrast agent, and no risk of nephrogenic systemic fibrosis is recommended and will be used in this study [20]. The outcome is the percentage semi-annual change in TKV measured by MRI, which will be performed at visit 1, visit 2 (24 weeks after visit 1), and visit 8 (24 weeks after visit 2) to observe the growth in kidney volume before and after the intervention.

Items to be measured and the time points of data collection are listed in Table 2.

**Table 2 Tab2:** SPIRIT table: Measurement items and time points of data capture

Items	Screening	Baseline	Treatment						Follow-up
	Visit 1	Visit 2	Visit 3	Visit 4	Visit 5	Visit 6	Visit 7	Visit 8	Visit 9
	−24 weeks	0 weeks	4 weeks	8 weeks	12 weeks	16 weeks	20 weeks	24 weeks	48 weeks
General									
Informed consent	×								
Inclusion and exclusion criteria	×								
Collect general information	×								
General physical examination	×								
Urine hCG (only women)	×								
Medical and drug use history	×								
Concomitant disease and treatment	×								
Combined medication	×	×	×	×	×	×	×	×	×
Effectiveness observation									
Vital signs	×	×	×	×	×	×	×	×	×
TCM symptoms	×	×	×	×	×	×	×	×	×
Pain evaluation	×	×	×	×	×	×	×	×	×
Renal function (eGFR, Scr, BUN)	×	×	×	×	×	×	×	×	×
MRI (TKV)	×	×						×	
Blood electrolytes	×	×			×			×	×
Urine β2-MG, mALB/Cr, RBP	×	×						×	×
Safety observation									
Blood test ^#^	×	×			×			×	×

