Urine test	×	×	×	×	×	×	×	×	×
Stool routine and occult blood test	×	×			×			×	×
Liver function (ALT, AST, γ-GT)	×	×			×			×	×
Electrocardiogram	×	×						×	×
Other data									
Adverse events			×	×	×	×	×	×	
Allocation		×							
Drug distribution		×	×	×	×	×	×		
Drug recycling			×	×	×	×	×	×	
Drug count			×	×	×	×	×	×	
Research conclusion								×	×

Each visit allows a window of 3 days

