### Trial status

The research strategy and study protocol were developed between October 2017 and June 2019. From October 2018 to July 2019, patients were screened and TKV was measured by MRI 24 weeks before the baseline. The follow-up visits and data analysis will take place from July 2019 to December 2020.

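### Table 2 schedules the only pregnancy test 24 weeks before first dispensing, although eligibility requires a negative test within 24 hours of dosing

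*Protocol article*

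**What the plan says.** The Inclusion criteria of the protocol article require a negative "urine or serum pregnancy test within 24 h prior to administration of YNF and agrees to use contraception throughout the study". The limit is tied to the moment of dosing and not to a visit.

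Table 2, under Measurement items and time points of data collection, sets the visit schedule:

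- The row "Urine hCG (only women" and the row "Inclusion and exclusion criteria" each carry one cross, at Visit 1 (screening, 24 weeks before baseline).
- Allocation is crossed at Visit 2 (week 0) only. "Drug distribution" is first crossed at Visit 2.
- The footnote reads "Each visit allows a window of 3 days".

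The Randomization section describes assignment as follows: "After screening, if the patient agrees to participate and voluntarily signs the informed consent form", the independent physician gives the patient a number. It mentions no pregnancy test or eligibility check at that point. Trial status reports the run-in as carried out: "patients were screened and TKV was measured by MRI 24 weeks before the baseline".

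**The concern.** The criterion asks for a test taken almost at the moment of dosing, while the schedule places the only test about half a year earlier. A woman can be negative at Visit 1, conceive during the 24-week run-in, and reach allocation without any scheduled item that would detect it.

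Two things are at stake. The first is safety: patients from 18 years of age are eligible, the product contains 17 herbal ingredients taken twice daily for 24 weeks, and the article gives no data on its safety in pregnancy. That does not show fetal harm, but it is why the protocol's own safeguard has to work. The second is compliance: a woman tested only when Table 2 says so does not meet a written inclusion criterion, and the withdrawal criteria remove participants who breach key eligibility criteria. The article does not say whether this criterion counts as key.

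**Working it through.** **Inputs.** Limit between test and dose: 24 h (Inclusion criteria). Scheduled hCG test: Visit 1 only (Table 2). Allocation and first dispensing: Visit 2 (Table 2). Interval between the two visits: 24 weeks, given in the column heads of Table 2, repeated in the text on MRI timing, and consistent with Trial status. Visit window: 3 days (Table 2 footnote).

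**Scheduled gap.**

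- Nominal: 24 × 7 = 168 days; 168 × 24 = 4,032 h.
- The footnote gives no direction for the window. Assume the widest reading, plus or minus 3 days at each visit.
- Shortest: 168 − 3 − 3 = 162 days; 162 × 24 = 3,888 h.
- Longest: 168 + 3 + 3 = 174 days; 174 × 24 = 4,176 h.
- 3,888 / 24 = 162, so even the shortest gap is 162 times the limit. Any narrower reading of the window stays closer to 168 days.

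**Could another scheduled item serve?**

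| Item in Table 2 | Crossed at Visit 2? | Covers pregnancy? |
|---|---|---|
| Urine hCG | No | Yes |
| Eligibility check | No | Would prompt the test, but is crossed at Visit 1 only |
| Urine test | Yes, as at every visit | No; a separate safety row, listed apart from hCG |
| Blood test | Yes | No; the footnote defines it as red cells, white cells, hemoglobin and platelets |

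The table does mark items repeated at Visit 2, such as renal function, MRI and liver function. The hCG row is not among them, and the text schedules no pre-dose test elsewhere.

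**Women who would need the test.** The article does not give this number. Assume that 40–60% of the 72 patients are women and that 10–50% of those are of child-bearing potential:

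- Low: 72 × 0.40 × 0.10 = 2.9, about 3.
- High: 72 × 0.60 × 0.50 = 21.6, about 22.
- Allocated to YNF at 1:1: 2.9 / 2 = 1.4 to 21.6 / 2 = 10.8, about 1 to 11.

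These are women to be tested, not women expected to be pregnant. The finding does not rest on these counts.

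**The case against.** The strongest reply is that nothing here is contradictory. The criterion is stated correctly, patients must satisfy it to be enrolled, and a test at Visit 1 does not rule out another at Visit 2. A site that reads the criteria will test just before dosing; harm arises only where a site works from the table alone. The article also condenses a fuller protocol whose visit instructions may include the test, and silence in a paragraph on randomization proves little. The contraception agreement, on a natural reading, covers the run-in, so few if any women would be pregnant at Visit 2. Finally, with screening from October 2018 to July 2019, some women had probably been allocated by the time the article appeared.

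Much of this stands, and it limits the severity. Both instructions can be followed, the number of pregnancies at stake is unknown and probably small, and the remedy reaches only women not yet allocated. It does not remove the defect. The article does not leave the timing to another document: it prints a 24 h rule and a schedule with a dedicated hCG row, and that row cannot satisfy the rule. The criterion asks for contraception and a test together, so one was not meant to replace the other.

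**Conclusion.** The concern holds. As printed, no scheduled pregnancy test meets the 24 h criterion: the only one falls 168 days before first dispensing, or 162 to 174 days on the widest reading of the visit window. The rule itself is sound; the schedule fails to carry it out.

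This should be fixed as a moderate matter of safety and eligibility. It has no bearing on sample size, power or the primary analysis. The conclusion depends on the positions of the crosses in Table 2, which are readable, and on the 24-week interval. It does not depend on the assumed share of women of child-bearing potential, and it does not claim that sites in practice omitted the test.

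**What to change.** In Table 2, add a cross at Visit 2 for a urine or serum hCG test, together with a brief re-check of eligibility. Require a negative result to be recorded before allocation and dispensing. Because doses are taken after breakfast and after dinner, and the first may be taken at home, tell the woman to take it within 24 h of the test. The rule should apply in both arms, since the allocation is blinded. The Visit 1 test can stay as a screening test. Apply the change to every woman not yet allocated.

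The cost is one extra cross for the test, one for the re-check, and one inexpensive test per woman concerned at a visit that already takes place. The criterion already demands the test, so no new burden is created in principle.
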